### Blinding

Action-RESPOND is an open trial, and no blinding was possible due to the nature of the intervention. Therefore, those receiving the intervention were not blinded to group allocation; however, the statistician conducting the data analysis will remain blinded.

### Intervention

#### The systems thinking child obesity prevention initiative (RESPOND trial)

As part of RESPOND, all communities received eight support sessions to build their capacity to deliver a series of three GMB workshops locally with key stakeholders in their communities. GMB is a qualitative, facilitated process, where a range of stakeholders create a visual map to build a shared understanding of obesity. The visual diagrams built as part of this process are called causal loop diagrams (CLDs) and they were developed on a software created by the research team (STICKE; Systems Thinking in Community Knowledge Exchange) [40] (see Fig 2 for an example). CLDs represent the variables participants perceive to be contributing to a problem and the causal connections between them. The CLDs are then used to help identify action ideas that are contextually appropriate to their community [22].

**Fig 2 pone.0302047.g002:**
[figure not shown]
Example causal loop diagram (CLD) from RESPOND built in partnership by local organisations and community stakeholders from Towong Shire, Victoria, Australia on the factors driving community health.

The GMBs are facilitated by the ‘backbone team’ within each community, who members are defined as those who have the authority and responsibility to make changes that affect the determinants of health within the community. The ‘backbone team’ consists of a combination of community development workers from local councils, health promotion practitioners from relevant health services and relevant non-government organisations in the region. By the end of the third GMB workshop (i.e., GMB3), multiple actions to address the identified variables in the CLD are generated by participants and these form the target of the implementation strategies below. The specific actions varied from community to community, however they broadly targeted community efforts to improve physical activity and nutrition in young children. Examples of some action ideas included community gardens, school-based cooking classes, efforts to improve the built environments (i.e. water fountains, paths), and increasing community participation and exposure to different sporting events and sporting infrastructure.

### The multicomponent implementation strategy (Action-RESPOND)

*Theoretical approach*. We applied the PARIHS (Promoting Action on Research Implementation in Health Services) framework [41] to support planning and development of the multicomponent implementation strategy (Action-RESPOND). This framework was selected as it focuses on capacity building and iterative tailoring of support, which is consistent with community-led approaches. PARIHS suggests that successful implementation occurs where there is a strong alignment between evidence, context and facilitation [41]. Specifically, it indicates that development of actions should consider ‘evidence’ that is contextually relevant and appropriate to the community, and implementation support is primarily delivered via a skilled ‘facilitator/coach’, who is familiar with the unique challenges and needs of the community (i.e. ‘local context’) and adapts support accordingly [41].

Using the PARIHS framework, we identified key determinants and opportunities to support implementation of actions at the community level. This was done by undertaking a targeted search of the literature and drawing on previous interviews with communities [35, 42, 43]. From this, we mapped the findings to the domains of the PARIHS framework (see Table 1) and identified the following key determinants of implementation: i) Limited knowledge of the research evidence underpinning selected actions; ii) ensuring implemented action addresses the community’s preferences and needs; iii) Ensuring the evidence-based action is compatible with the community’s context and needs; iv) Lack of knowledge and skills on how to implement actions developed using systems thinking approaches, i.e. perceived feasibility and difficulty of implementation, and steps required to implement; v) Cultivating leadership that is supportive of implementation of action; vi) Having human and other resources to drive implementation in local community; and vii) Establishing community culture that is receptive to and supportive of implementation of action.

**Table 1 pone.0302047.t001:** Determinants to implementation identified in the evidence and context domains of the Promoting Action on Research Implementation in Health Sciences (PARIHS) framework, with corresponding implementation strategies and details of delivery.

Determinants (as identified using the PARIHS framework)	Implementation Strategy (Action)^1^	Implementation Strategy delivery ^a^: • *Actor (who is delivering)* ^*b*^ • *Context (delivery method)* • *Target (who is receiving it)* ^*b*^ • *Time (duration & frequency of delivery)*
**Evidence**		
Limited knowledge of the research evidence underpinning selected actions.	Increasing awareness and knowledge of research evidence supporting the effectiveness of actions generated during GMBs: i) Evidence brief presentation on actions generated in GMBs, which the community is most interested in. ii) Evidence summary on community-based childhood obesity prevention interventions	Actor: research team
		Context: i) Presentation during GMB3 debrief (online meeting) ii) Recorded presentation
		Target: backbone team
		Time: i) After GMB3; approx. 15-minute presentation during 2-hour meeting ii) Between GMB3 and Edu Workshop; approx. 20-minute presentation
Ensuring implemented action addresses the community’s preferences and needs.	i) Multiple sense-checks during selection of action and goal setting, to ensure it aligns with community’s preferences (as expressed by community members during GMBs) ii) Embedding processes in action plan, to involve community members in implementation of action and to feedback progress of action to wider community	Actor: research team
		Context: i) Edu Workshop—action prioritisation and SMART goal planning activity ii) Edu Workshop—Action planning activity
		Target: backbone team
		Time: i) Edu Workshop (face-to-face, 6-hour) ii) Edu Workshop (face-to-face, 6-hour) and prompt during check-in sessions
Ensuring the evidence-based action is compatible with the community’s context and needs.	Building capacity to prioritise and select action with consideration of research evidence and local context information, using the Hexagon Tool ^c^	Actor: research team
		Context: Edu Workshop—action prioritisation activity
		Target: backbone team
		Time: Edu Workshop (face-to-face, 6-hour)
Lack of knowledge and skills on how to implement actions developed using systems thinking approaches, i.e. perceived feasibility and difficulty of implementation, and steps required to implement.	i) Building capacity to identify locally relevant enablers and barriers to implement selected priority action ii) Increase knowledge on implementation strategies and support action planning iii) Support problem solving (tailored to each individual community) during implementation process	Actor: i) Research team ii) Research team iii) Implementation Coach
		Context: i) Edu Workshop–change over time and implementation CLD building activity ii) Edu Workshop–provision of training and resources (implementation tools and action plan template) and demonstrate application iii) During check-in sessions
		Target: i) Backbone team ii) Backbone team iii) Implementation Champion/s
		Time: i) Edu Workshop (face-to-face, 6-hour) ii) Edu Workshop (face-to-face, 6-hour) iii) Check-in sessions (online meeting, 1.5 hours, approx. 2-months apart)
**Context**		
Cultivating leadership that is supportive of implementation of action.	Inform and engage key decision-makers, including health service managers and local council members	Actor: i) Implementation Coach ii) Research team lead
		Context: i) Invite key decision-makers to attend Edu Workshop (via email) ii) Quarterly presentation to RESPOND leadership/ stakeholder group, providing update on Action-RESPOND
		Target: i) Key decision-makers in the community ii) Key decision-makers in the community
		Time: i) Prior to Edu Workshop ii) RESPOND Partnership Group Meeting (online, occurs quarterly)
Having human and other resources to drive implementation in local community.	Identify and formalise role of Implementation Champion in each community	Actor: Implementation Coach
		Context: Position description circulated via email and formalise at Edu Workshop
		Target: Backbone team
		Time: Edu Workshop
Establishing community culture that is receptive to and supportive of implementation of action.	i) Involve community members in the GMB process ii) Ensure continued feedback to community regarding progress of action implementation	Actor: i) Research team ii) Implementation Coach and Implementation Champion
		Context: i) GMB workshops ii) Establishing these processes during Check-in sessions
		Target: i) Community members and stakeholders ii) Community members and stakeholders
		Time: i) GMB workshops ii) Check-in sessions (online meeting, 1.5 hours, approx. 2-months apart)

^a^ Based on Presseau et al 2019.

^b^ Actors and Targets: a) Backbone team–comprised of community development workers from local council, health promotion practitioners from local health services/ non-government organisations in each community; b) Implementation Champion/s–identified as key representative from the backbone team; c) Research team–comprised of systems science experts (AB, JH), implementation scientists (SY–team lead; [name]) and Implementation Coach (MH); d) Implementation Coach (MH)–situated in and has extensive experience working in health promotion within targeted communities.

^c^ Based on Metz et al 2019.

Abbreviations: GMB–group model building; GMB3 –the 3^rd^ group model building workshop of the RESPOND trial; CLD–causal loop diagram.

*Delivery modality*. Action-RESPOND consist of seven implementation strategies that will be delivered over approximately 9-months via one online meeting (GMB3 debrief), one face-to-face group education workshop (Edu Workshop), two formal facilitation contacts delivered by an implementation coach (Check-in sessions) and local tailored support as requested. Additionally, we will incorporate system science concepts, including qualitative systems mapping, use of reference modes (which capture the dynamic nature of key factors within a system) and feedback loops, during the delivery of the multicomponent implementation strategy (see Table 1). The research team delivering the intervention consists of systems science experts (AB, JH) and implementation scientists (SY, [name]) and an Implementation Coach (MH). The Implementation Coach (MH) has 10 years of health promotion experience working within the targeted communities and is situated within one community of the Ovens-Murray region.

The Edu Workshop will be delivered face-to-face to the ‘backbone team’ who consist of community development workers from local councils, health promotion practitioners from relevant health services and relevant non-government organisations in the region. This session will be co-facilitated by systems science (AB) and implementation science (SY) experts together with the Implementation Coach (MH).

The Implementation Coach (MH) will be primarily responsible for delivering the two facilitation check-in sessions. The sessions will either be delivered over videoconference call or face-to-face (depending on preference of community) with identified Implementation Champion(s) within each community. The Champion/s are likely to consist of one or multiple individuals (in the instance of shared role or part-time staff) who are health promotion officers within the local community health teams or local council.

*Description of implementation strategies*. Consistent with the PARIHS framework, we will primarily use an implementation facilitation approach to deliver specific strategies. Implementation facilitation is a multi-faceted process to enable communities to develop processes, relationships and structures to increase implementation and address key identified local gaps [44]. The selection of implementation strategies was overseen by an advisory group consisting of implementation scientists, system scientists, and health promotion and community development experts. The strategies were intentionally selected to address the determinants identified in Table 1, based on evidence of effectiveness from a systematic review of facilitation strategies [45] and described using the Action, Actor, Context, Target, and Time framework [46]. The implementation strategies were piloted with one community and amendments made to refine content. The refined implementation strategies, which will be delivered, are described below.

### 1. Generation and provision of evidence-briefs and local data

Following GMB3, a presentation of the evidence for the actions that have emerged will be provided by the research team. This will be accompanied by local data on potential reach of such actions and the extent of local implementation where available. This will be briefly presented at an online meeting and a discussion around the actions (GMB3 debrief), facilitated by a member of the research team. Additionally, prior to the Edu Workshop, a recorded PowerPoint presentation summarising reviews on effectiveness of community-based childhood obesity prevention interventions are circulated to the backbone team of each community.

### 2. Support prioritisation of evidence-based and locally appropriate innovations

As many actions are generated via the GMBs, communities will be subsequently supported to prioritise actions for implementation. At the Edu Workshop, the Hexagon Tool [47] will be used to support the prioritisation of actions identified. Prioritisation will be achieved by a discussion around the following elements regarding their key actions: capacity to implement, the evidence surrounding the intervention, fit with current policy environment and existing initiatives, how well it addresses local needs, usability and existing support systems. This prioritised action will form the behavioural target of the subsequent implementation strategies. Although the backbone team will be asked to prioritise and focus on a single action, it is acknowledged that other actions led by community members or groups may also be implemented at the same time, recognising the broader community engagement with this process.

### 3. Establish processes to feedback action to community and continue to engage community members

Building on the inherently participatory processes of the GMBs and existing community engagement, the Implementation Coach will continue to work with Implementation Champion/s (see #4) to establish mechanisms to continue to engage with community members. This may include timely reporting on the key actions following GMB processes, communicating an update on implementation activities, and creating feedback mechanisms as appropriate, considering reach and accessibility (i.e., follow up emails, surveys, social media updates, newsletters, reports). Each community will be supported to develop a communication plan.

### 4. Selection of implementation champion/s

The use of champions can enhance implementation through various mechanisms including trust-based relationships, role modelling and advocacy [48]. An Implementation Champion (or multiple) will be identified by each community’s backbone team prior to the Edu Workshop. A position description for the Champion will be provided outlining the expectations for the role. This includes supporting the development and implementation of an action plan (see 5c), mapping the implementation processes on STICKE and monitoring implementation progress.

### 5. Provide training that is dynamic and applied

The Edu Workshop will be undertaken with each community’s backbone team. The training will specifically target barriers related to knowledge and skills identified by health promotion teams within the communities and focus on increasing capacity to support implementation of the prioritised action. The session is designed to be interactive; incorporating group discussions, real world examples and Group Model Building activities around implementation of the priority action. It will include the following strategies:

5a. Goal setting

The research team will support the participants with generating a SMART (Specific, Measurable, Achievable, Relevant and Time-bound) goal related to the prioritised action, that is considered timely, practical and feasible to achieve in the next 6–9 months. This will be transferred across to their action plan (see 5c).

5b. Qualitative systems methods to visualise the processes of change, support participants to identify determinants of successful implementation of action

The systems science expert (AB) will undertake a change over time activity to support participants to visualise how changes in the prioritised action would have looked like in the past, in the future, and if active steps were /were not taken to implement the action. The resulting “reference mode” is a visual method used in system science, describing how a key outcome of interest behaves or operates under different conditions, or in response to various inputs or changes in the context of a system’s structure (I.e., policies, culture, and infrastructure) [19]. This will be used to support the identification of determinants of successful implementation of action (i.e., what needs to be done to avoid/achieve such trends). This is supplemented further by applying relevant implementation science theories. The specific theory will be determined by the implementation science expert (SY) pending action selection and community context, however could include the Theoretical Domains Framework [32], the Consolidated Framework of Implementation Research [31] or the EPIS framework [49]. Once the barriers have been identified and prioritised, the group will be supported to generate a systems map using the STICKE software, creating a CLD outlining determinants to implementation. This will reflect the adaptive nature of implementing action, drawing feedback loops to describe how a system responds to changes in conditions resulting from implementing action/s.

5c. Action planning

Lastly, the training will support participants with identifying specific strategies to address key determinants and this will be used to populate an action plan. The action plan will outline the specific activity, who will be responsible for implementation, the timeframe for implementation, and the resources required. Both the CLD for implementation and the action plan developed during this education session will be visually presented on STICKE and used in the Check-in sessions to support tracking of activities in the action plan.

### 6. Tailor facilitation approach to individual communities

In the Check-in sessions with the Implementation Champion/s, the Implementation Coach will support the ongoing assessment of implementation context, tailoring of the intervention to suit local context, ongoing monitoring of progress and outcomes, and identify ways to continue community engagement. The Check-in session will begin with a review of the implementation CLD generated in the Edu Workshop, to track progress made with each action plan activity, and record any adaptations made to the action plan. Throughout the session, the Implementation Coach will provide positive reinforcement, facilitate reflection and problem solving. The discussion will be an opportunity to update the action plan, ensuring that it contains required activities to achieve the SMART goal and set new activities, goals or actions if required. The support will be tailored according to the preferences, needs and/or barriers of each community. The Implementation Coach is available to be contacted for additional local tailored support throughout the intervention period. All support provided including each contact, attendees, duration and nature of support will be captured using a Microsoft Excel spreadsheet.

### 7. Inform and engage leadership

Health promotion, allied health and relevant local council managers will be invited to the GMBs and face-to-face Edu Workshop. This is to generate leadership support for the process, interventions and decisions around action planning made by the backbone team. Further, quarterly updates will be provided by the research team lead (SY) to the leadership group around the progress of the activities related to the research, with an attempt to support buy in and promotion of the Action-RESPOND program. The leadership group consists of the research team along with key RESPOND partner organisations, including the Department of Health, the Victorian Department of Education, management from local community health services, VicHealth and regional Local Council representatives.

*Control group*. Communities in the control group will receive usual care as part of RESPOND, including regular updates, networking opportunities, and implementation support as requested via e-mail and phone.

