### Potential co-intervention and contamination

At follow-up, we will assess if communities received any other support or new funds to implement their actions (outside of the research team) and to describe this support. Additionally, we will assess the extent of contamination in participants of the control communities, by asking whether they have received any component of the Action-RESPOND program and any other support to deliver the proposed initiatives.

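### The quarterly leadership update, one of two parts of the leadership strategy, is given in a forum shared by both arms, and the contamination question is not put to the decision-makers it targets

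*Protocol article*

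**What the plan says.** Strategy 7 (Inform and engage leadership) has two parts.

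- **Part (i)** is an invitation: health promotion, allied health and "relevant local council managers will be invited to the GMBs and face-to-face Edu Workshop". Table 1 lists only the Edu Workshop invitation under this part.
- **Part (ii)** is given in Table 1 as "Quarterly presentation to RESPOND leadership/ stakeholder group, providing update on Action-RESPOND", with the timing entry "RESPOND Partnership Group Meeting (online, occurs quarterly". The target of both parts is "Key decision-makers in the community". The text of strategy 7 says that the updates are made "with an attempt to support buy in and promotion of the Action-RESPOND program".

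The leadership group is described by type of organisation: the research team, state departments and other RESPOND partners, including "management from local community health services, VicHealth and regional Local Council representatives".

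Under Trial design, the five control communities are to have no added implementation support. The control-group paragraph reads "Communities in the control group will receive usual care as part of RESPOND, including regular updates, networking opportunities", together with support on request by e-mail and phone.

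Under Potential co-intervention and contamination, participants of the control communities are assessed at follow-up by "asking whether they have received any component of the Action-RESPOND program" and any other support. Eligibility criteria names the backbone team of each LGA as the main participants.

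**The concern.** Part (ii) is more than research reporting. Its stated purpose is to win support for the program, and Table 1 sets it against a named determinant, leadership that backs implementation. It is therefore an active element of the package under test, yet it is delivered through a forum of the parent study, in which both arms take part.

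The pilot's first aim is to gauge the potential impact of the strategies on fidelity. If leaders of control LGAs receive part of the package while outcomes accrue, the comparison is no longer the full package against usual care. If the contamination question also misses that exposure, a small or absent difference could be read as weakness of the package when part of it had been shared.

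**Working it through.** The plan gives no sample size calculation, effect size or SD, so there is no figure of its own to reproduce. The check sets the relevant sections side by side.

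1. **Is the channel shared?** Table 1 names the RESPOND Partnership Group Meeting. Context and setting says that all ten communities received RESPOND. The group includes state departments and VicHealth, whose remit necessarily covers both arms, and local health service management and council representatives with no restriction to intervention LGAs. The article mentions no separate session or closed item. The Dissemination plan also refers to existing network meetings attended by all LGAs, so joint forums are part of how the study runs.

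2. **Is the content active?** Yes, by its stated purpose (buy-in and promotion) and by its place among the seven strategies in Table 1.

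3. **How much is shared?** One of the two parts of one of the seven strategies. With quarterly updates and the roughly nine months from baseline to follow-up given under Trial design, 9 / 3 = about 3 updates. Up to 5 of the 5 control LGAs could be exposed; how many would be is not stated.

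4. **Could it move an outcome?** Fidelity is the sum of three items scored 1 to 7. One item rates how engaged organisations and individuals are with implementation. The sum runs from 3 to 21, a range of 18, and the engagement item supplies 7 − 1 = 6 of those points, or one third. Leadership support in a control LGA could plausibly raise that item. One representative per community reports fidelity, so the regression rests on five communities against five.

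5. **Would the contamination question detect it?** The target in Table 1 is decision-makers. The respondents are control-community participants, chiefly backbone team members. No question to leadership-group members is described. Strategy 6 logs contacts and attendees for the coach's support, but no such log is stated for the partnership meetings.

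6. **Direction.** Any effect of part (ii) in control LGAs would raise control scores and narrow the between-group difference. Its size would require the share of the package effect due to part (ii) and the number of control LGAs exposed. The document gives neither.

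**The case against.** The strongest case on the other side has five parts.

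- **Exposure is inferred.** The leadership group is listed by organisation type, not by LGA, and a journal article may leave membership and agendas to the full protocol. It would go too far to say that the update reaches control-area managers by design. What stands is that a RESPOND-wide forum is named as the delivery channel, that its statewide members span both arms, and that no separation is described.
- **Only part of the strategy is shared.** A reader might infer that the whole leadership strategy goes to both arms. The document does not support that: the Edu Workshop is an Action-RESPOND event, so the invitation to it is tied to intervention communities.
- **The dose may be weak.** A control-area manager who hears the update gains no workshop, action plan, Champion or Check-in session. Nor does the article say that the control arm's regular updates carry Action-RESPOND content. This is fair, and it limits the likely size.
- **The contamination question is not blind to this route.** Backbone members are defined as having authority to make changes and come from councils and health services, as do some leadership-group members. The question covers any component and other support, and communities are also asked about new funds. To say that respondents would not see the exposure is therefore too strong; the question may under-detect it.
- **The decision at stake is a judgement.** Progression is decided by majority on acceptability and feasibility, not by a between-group test. That lowers the stakes, but fidelity and adoption data feed that decision and will also be reported as a comparison.

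**Conclusion.** The point holds for part (ii) of strategy 7. A component meant to win leadership support is delivered in a forum common to both arms, with no separation described. This sits badly with a control arm said to receive no added implementation support. The contamination question is not directed at the people this component targets.

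The likely consequence is some dilution of the fidelity and adoption contrast. This rests on two assumptions: that some leaders of control LGAs attend or hear the updates, and that leadership support affects implementation locally. The first is a strong inference and the second is the premise of the strategy itself; neither is shown.

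A reader might try to size the dilution by giving the seven strategies equal, additive weight: 6/7 = 86% of the effect retained if the whole leadership strategy were shared, or 6.5/7 = 93% if half of it were. The document supports neither figure. It gives no weights, and the first wrongly counts the Edu Workshop invitation as shared.

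For a ten-community pilot this is a worthwhile, inexpensive improvement. It does not undermine the trial.

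**What to change.** 1. Until the follow-up survey closes, give the promotional Action-RESPOND update only to leaders of the five intervention LGAs, in a separate session or a closed agenda item.
2. Where an organisation spans both arms and cannot be separated, as with the state departments and VicHealth, list this part in Table 1 as common to both arms and not as part of the tested contrast.
3. Record attendance at these meetings by LGA.
4. Put the existing contamination question to control-area managers as well as to backbone team members.
5. Report the attendance record and the managers' answers beside the between-group comparison of fidelity and adoption.

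If some joint updates have already been given, items 2 to 5 still apply and would keep a small difference from being misread.

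The cost is the logistics of splitting about three online updates, an attendance list and a few more survey respondents, with no extra staff. The one downside is that control-area leaders hear about the program later.
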